## **III / Food taboos**

- In your village, what are the food prohibitions / taboos (animal meat, cereals, fruits, leaves, etc.) (name it / them and give the reasons)
- In your family, what are the food prohibitions / taboos (animal meats, cereals, fruits, leaves, etc.) (name them and give the reasons)
- What foods should you not eat in your community? (Name it / them and give the reasons)

## **IV Collection of RUTF**

- What do you think of RUTF?
- How do you compare the effectiveness of RUTF compared to traditional products?

Are RUTF compatible with the treatments you give against malnutrition (how?)

## **Focus Group**

## **Annex 4.5. Focus Group Guide**

Targets:

- Mothers of SAM children on RUTF
- Men of the general population
- Women in the general population

### **Identification**

- Dated
- Num FG
- CSPA
- Group

### **I / Perception of malnutrition (manifestations, causes, consequence and treatment)**

- What is malnutrition?
- How does it manifest itself?
- What do you think are the causes?
- How are children with malnutrition treated (traditional treatment)?
- Who will you see for your child if they are malnourished?
- What foods and drugs do you use to treat them?
- Do you think that we can cure malnutrition?
- What treatment have you found to be the most effective for your child's malnutrition?

### **II / Collection of RUTF**

- What are the different types of RUTF that you know of? (Probe " RUTF 'red' = Plumpy'Nut and ASPE orange = Plumpy'Sup?)
- What is the difference between the two?
- What do you think of RUTF? What are the different ways to get RUTF? If the RUTF market, what are the selling prices?
- What are the words of the mother towards her child / other children around RUTF?
- What do RUTF contain?
- In which case / disease would you give RUTF to your child?
- Have you observed any positive effects of RUTF on children (not malnourished)?
- Have you observed any negative effects of RUTF on children (not malnourished)?
- Have you observed any positive effects of RUTF on malnourished children?
- Have you observed any negative effects of RUTF on the health of malnourished children?
- Do RUTF have positive effects sought / appreciated by other family members (especially adults)?
- Can RUTF be considered as normal foods / ingredients (reasons, desired effects)?
- What are the perceptions around RUTF ruptures?
- What about the amounts of RUTF given to children (insufficient, enough, too much)
- If we gave less, what do mothers think? (efficiency)

### III / Use of RUTF

- How easy is it to give RUTF to children?
- What time of day is RUTF given; before or after other foods? Before or after breastfeeding?
- Where is the sachet stored during the day? Who could have access to it?
- Have you observed any difficulties in administering RUTF to your children?
- What are the quantities (sachets) consumed by the children per day (Probe: recommended quantity, less than recommended quantities, more than quantities)?
- Do you know how the number of RUTF sachets given to you was determined? (Why were you given this number of bags? Why has this number increased since the last time? Etc...)
- In how many days is the quantity received for a week consumed? Is it different during Ramadan? during the lean season? etc.
- Do you know the difference between RUTF 'red' (Plumpy'Nut) and ASPE orange (Plumpy'Sup)?
- If the child consumes less than expected, what use is made of the uneaten sachets or the remains of the opened sachet?
- Does it happen that RUTF sachets are shared with the siblings of the sick child or with other family members (reasons for sharing)
- In what form does the child like RUTF (probe mix in porridge? In bread? Diluted in water)
- Does RUTF make the child thirsty? What drink does the child take with it?
- Does the child accept well to eat again the family dish after several weeks on the RUTF diet? or does it make difficulties? What are the strategies of mothers then so that the child eats the family dish?

### IV / Child feeding under RUTF

- What other foods are given to sick children on RUTF?
- Have you observed any effects of these foods on the weight gain of the child? If yes, which ones ?
- In what situation do you give other foods to your child on RUTF?
- How effective are these foods compared to RUTF?
- For a child on RUTF, when are other foods introduced in his diet?
- Does the child latch on while being treated with RUTF? If so, before or after RUTF? how many times per day is the child breastfed while being treated with RUTF?
- Does breast milk affect the child's uptake of RUTF? If yes which ?
- Does RUTF (or treatment for malnutrition) affect breast milk intake? If yes which ?
- How do you feel about breast milk when the child is malnourished?
- How does breastfeeding work when the child is malnourished and has no RUTF?
- What positive effects have you observed of breastfeeding on the consumption of RUTF by the child?
- What negative effects have you observed of breastfeeding on the consumption of RUTF by the child?

## Annex 4.6. Home observation grid

**Indication:** The investigator will stay a whole day in a household to note all the facts relating to the food consumption of children under RUTF.

The interviewer will be content to observe what is happening in the household with the help of the observation guide. It should remain neutral as much as possible without interfering in the actions and interactions observed. In case, for one reason or another, the investigator intervenes in the observed sequences, this should be clearly noted in the observation report.

### Sequence description

**Specify: Sequence observed**

**Place date .....**

**Observed people**

**Child's age**

**Mother's age. .... Mother's level of instruction**

- |                                         |                                                                                                                                                                                                                                                                                                                                                                                                                                                                                                                                                                                                                                                              |
|-----------------------------------------|--------------------------------------------------------------------------------------------------------------------------------------------------------------------------------------------------------------------------------------------------------------------------------------------------------------------------------------------------------------------------------------------------------------------------------------------------------------------------------------------------------------------------------------------------------------------------------------------------------------------------------------------------------------|
| RUTF consumption                 | 

• Where are the RUTF kept (ask the mother at the end of the observation)?

• When are the RUTF given to the child? (Does the mother breastfeed the child first?)

• What are the quantities given at each moment and per day?

• How the child reacts (does he accept or not, asks for more?)

• How does the mother manage to get the child to take RUTF? (Is the child left alone to consume it?)

• Are there minimum hygiene rules followed before consuming RUTF? : hand washing, drinking water in a clean container / bowl consumed by the child while taking RUTF

 |
| Consumption of other foods       | 

• What other foods are given to the child? (specify the form: solid, liquid, etc.)

• When are these foods given? (before / after RUTF?, at mealtimes? ...)

• Is it a food prepared for the child or taken from the family dish

• How much is given to the child (the unit will be that used by the mother: spoon, large or small ladle ...)

• How much of these products compared to RUTF (smaller, larger, or even

• Are these foods given at the same time as RUTF or at other times

• How children react to these foods (like or dislike)

                 |
| Sharing of RUTF in the household | 

• Who else uses RUTF in the household?

• Does the mother drip when she gives the child (how much?)

• What use is made of the rest of the RUTF when the child does not consume the whole tablet?

• How other children react when the sick child is given RUTF (crowding around or indifference)

• How does the mother of the child react when the other children obviously want the sachets?

                                                                                                                                                                                  |

## **Annex 5: Economic evaluation**

### **1. Context and rationale**

The present work is a sub-study nested within a clinical trial measuring the effectiveness of the reduced dose of RUTF in the management of SAM without medical complications. The study will take place in the Health Zones (ZS) of Nzaba and Bonzola in the province of Kasai Oriental in the Democratic Republic of Congo (DRC). This province experienced a great conflict between the militia of Kamwina Nsapu and the regular army of the DRC. The consequences of this conflict had very serious influences on the nutritional situation of children under 5 in the province. More than 30% and 33% of them suffer from malnutrition respectively in the ZS of Nzaba and Bonzola.

A cost-effectiveness evaluation in the context of a reduction in the dose of RUTF in the management of SAM children showed that the reduced dosage of RUTF was economically beneficial for the treatment of malnutrition. : the cost of treating a child from admission to discharge in the reduced dosage arm of RUTF was \$ 75 while the cost of treating a child with the standard dosage of RUTF was estimated at \$ 91 for an average length of stay of 8 weeks on both sides (N'Diaye et al, 2021). However, an economic evaluation of the reduced dose has never been evaluated without additional staff to collect the data. A comparative study of reduced dose treatment compared to standard treatment in real conditions presents an opportunity to perform an economic evaluation in parallel. The hypothesis is that this could lead to a reduction in costs per child treated. This is the reason why this evaluation is proposed in the ZS of Nzaba and Bonzola in the province of Kasai Oriental in the DRC.

### **2. Goals**

#### **2.1.Main objective**

To assess from a societal point of view, the economic cost of treating children with SAM without medical complications with a reduced dose of RUTF compared to treatment with a standard dose.

#### **2.2.Specific objectives**

The specific objectives of this study are:

- Estimate the costs from a societal point of view, including the costs borne not only by ACF and its partners but also by the beneficiaries of SAM treatment.
- Estimate the cost of SAM treatment for a child, with standard dose and with reduced dose
- Estimate the impact of a reduced dose on costs, taking into account its impact on efficacy results.

### **3. Methodology**

#### **3.1.Participants, interventions and outcomes**

##### **a.Study framework**

The present work is a sub-study of a clinical trial measuring the effectiveness of the reduced dose of RUTF in the management of SAM without medical complications. The study will take place in the Health Zones (ZS) of Nzaba and Bonzola in the province of Kasai Oriental in the DRC.

##### **b. Study population**

It will be made up of children aged 6 to 59 months admitted to SAM treatment & included in the trial, ie 500 SAM children in each arm.

##### **c.Type of economic evaluation**

This is a parallel economic evaluation of the clinical trial, based on a static decision tree type model simulating the trajectory of all children with SAM included in the trial. SIf the non-inferiority hypothesis is verified in the DRC context, the type of analysis will be a Cost Minimization Analysis, otherwise it will be a Cost Effectiveness Analysis.

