## **Research hypotheses**

### **Main hypothesis**

Children receiving the reduced dose will have the same weight gain from admission to discharge as children receiving the standard dose of RUTF with a non-inferiority margin of 0.5g / kg / day.

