### **Secondary assumptions**

- Children receiving the reduced dose of RUTF will have the same performance indicators (cure rate, death, drop-out, relapse) as those receiving the standard dose;
- Children receiving the reduced dose of RUTF will have the same length of stay as those receiving the standard dose;
- Children receiving the reduced dose of RUTF will have the same psychomotor development as those receiving the standard dose;
- Treatment with a reduced dosage of RUTF will be less expensive than treatment with the standard dose.

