### **2.3.3. Statistical analyzes**

For the quantitative part of the study, the data will be summarized in Mean and Standard Deviation if they are normally distributed (normality test) for continuous variables and in absolute and relative frequencies for categorical variables.

The t-test and the chi-square test will be used respectively to compare the means and the proportions of the socio-demographic characteristics at admission for the quantitative and qualitative variables.

Linear regression analyzes will be used to determine the significant differences between the 2 groups of children for the quantitative variables.

Binary logistic regression analyzes will be used to determine the significant differences between the 2 groups of children for the binomial qualitative variables (2 response modalities).

Multinomial logistic regression analyzes will be used to determine the significant differences between the 2 groups of children for the multinomial qualitative variables (3 or more modalities).

All analyzes will be done in an adjusted and unadjusted model and a difference is statistically significant when the P-value is less than 0.05.

The results will be analyzed using statistical software, in this case STATA, version 17.

The main analyzes will be done by intention to treat (ITT) and per protocol for the main result, in this case, the speed of weight gain. The other secondary results will be analyzed only by intention to treat (ITT).

For the DPM, a score will be assigned to the participant and the sum will constitute the total score for each participant per domain.

For focus group data, after transcription of the recordings into Word 2019, thematic analysis will be done using Excel tables (matrix) or Nvivo® software.

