##### **e.Efficacy data**

The cure rate among all children enrolled in the study, and per arm, will be the main outcome of interest for the economic evaluation. We will explore the cure rate per arm at the end of the 12 weeks maximum treatment, and also we will be able to evaluate the cure rate including the children referred to UNTI who return to UNTA and positively complete their treatment.

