#### **i. Expected results**

- a. Average cost per SAM child treated for a child on standard dose and on reduced dose
- b. If a Cost Minimization Analysis then we will obtain a percentage of the total cost of treatment under reduced dose compared to that of children in the control group;
- c. If a Cost Effectiveness Analysis then we will obtain a cost ratio per additional SAM child cured by the reduced dose approach

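### The economic evaluation drops the cure comparison from its result when the non-inferiority hypothesis is met, but that hypothesis concerns weight gain, while the evaluation's own main outcome is cure

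*Protocol*

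**What the plan says.** Five places in the protocol bear on this.

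- **The switch.** Annex 5, section 3.1 c (Type of economic evaluation): if the non-inferiority hypothesis is verified, "the type of analysis will be a Cost Minimization Analysis, otherwise it will be a Cost Effectiveness Analysis". No endpoint is named.
- **The non-inferiority hypothesis.** The Main hypothesis is about velocity, and it is framed "with a non-inferiority margin of 0.5g / kg / day". Sections 2.1.4 (Main result) and 2.1.6 (Sample size) use the same outcome and margin. No other outcome has a margin.
- **The economic outcome.** Annex 5, section 3.1 e (Efficacy data): "The cure rate among all children enrolled in the study, and per arm, will be the main outcome of interest for the economic evaluation".
- **How cure is tested.** The Secondary assumptions expect the arms to be the same: "Children receiving the reduced dose of RUTF will have the same performance indicators (cure rate, death, drop-out, relapse"). No margin is given. Section 2.3.3 treats binary outcomes by a difference test: "Binary logistic regression analyzes will be used to determine the significant differences between the 2 groups of children".
- **What each branch delivers.** Annex 5, section 3.1 i (Expected results): item (a) is the average cost per child treated in each arm. Item (b) is "If a Cost Minimization Analysis then we will obtain a percentage of the total cost of treatment under reduced dose" compared with control. Item (c), a cost per additional child cured, appears only in the cost-effectiveness branch.

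Annex 5, section 2.2 sets this objective: "Estimate the impact of a reduced dose on costs, taking into account its impact on efficacy results".

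**The concern.** Cost minimisation is a valid economic comparison only when the effects being bought are taken as equal. Here that premise would rest on a test of one outcome, weight-gain velocity, and be applied to another, cure. The two are related but distinct. Cure depends on weight-for-height, MUAC and oedema criteria being met within 12 weeks. Death, default and non-response count against cure but need not lower the velocity of the children who are measured.

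At stake is the economic conclusion, which is a main reason for studying a reduced dose. If the reduced dose were cheaper but cured fewer children, the economic result in the branch the sponsor expects would be a saving with no effect term beside it. The objective of taking efficacy into account would not be met in that branch.

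**Working it through.** **1. What the non-inferiority test covers.** Inputs from section 2.1.6: SD 2.6, margin 0.5, expected difference 0, one-sided alpha 0.05 (Z = 1.64), power 80% (Z = 0.84).

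n per arm = (Z₁₋α + Z₁₋β)² × 2σ² / Δ² = (1.645 + 0.842)² × 2 × 2.6² / 0.5² ≈ 335, which is the protocol's figure. The rounded Z values give 333. The calculation contains weight gain only; nothing in it refers to cure.

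**2. How often the switch selects cost minimisation.** Annex 5 gives 500 per arm; removing the planned 20% dropout leaves 400. With a true velocity difference of 0, the probability of showing non-inferiority is Φ(0.5 / SE − 1.645), where SE = 2.6 × √(2/n).

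| n per arm | SE | Probability |
|---|---|---|
| 400 | 0.184 | 0.86 |
| 500 | 0.164 | 0.92 |

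Cost minimisation is therefore the expected branch if the trial's main hypothesis is true.

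**3. What the expected branch omits.** Items (a) and (b) of section 3.1 i are costs. Item (c) is the only listed result that relates cost to cure, and it belongs to the other branch. Also, section 2.1.4 restricts the per-protocol velocity analysis to children declared cured, so that half of the primary comparison cannot register lost cures.

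**4. Illustration of size.** Costs per child treated are those cited in Annex 5, section 1, from the earlier evaluation: 75 dollars (reduced dose) and 91 dollars (standard). They are held fixed. The control cure rates and deficits are assumptions; the only cure figure in the protocol is a general remark in Annex 4 that outpatient cure often exceeds 75%.

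- Cost minimisation: 75/91 = 82.4% of control cost, a saving of 17.6%, whatever the cure rates.
- Saving per cured child, with control cure p and deficit d: 1 − [75/(p − d)] / [91/p].

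| Cure deficit | p = 75% | p = 85% | p = 90% |
|---|---|---|---|
| 0 points | 17.6% | 17.6% | 17.6% |
| 5 points | 11.7% | 12.4% | 12.7% |
| 10 points | 4.9% | 6.6% | 7.3% |
| 15 points | −3.0% | −0.1% | 1.1% |

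Example: p = 75%, d = 5 points gives 75/0.70 = 107.1 against 91/0.75 = 121.3 dollars per cured child, a saving of 11.7%. Five points is 25 fewer cures per 500 children.

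**The case against.** **Cure is not lost from view.** It is a clinical outcome analysed by intention to treat (sections 2.1.4 and 2.3.3), and Annex 5, section 3.1 e looks at it by arm without making that depend on the switch. Average cost per child treated, total cost by arm and by cost type, and best-case and less favourable sensitivity analyses are also planned. A reader might infer that a cure deficit would be ignored altogether, or that the only output would be one cost percentage. The documents do not support that. What stands is narrower: in the cost-minimisation branch, none of the listed results sets a cost difference against a cure difference.

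**Poorer outcomes partly enter the costs.** The model follows each child's trajectory, counts weekly visits and includes inpatient care for complications (Annex 5, sections 3.1 f and 3.2.2). This is correct, but a cost is not an effect. A child who leaves uncured is not counted as a lost cure.

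**Non-inferior velocity limits how far recovery can be delayed.** A reader might take the margin itself, 4.5 against 5 g/kg/day, and infer that children could need 5/4.5 = 1.11 times as long, 11% longer, with the switch still made. On the one-sided 5% test implied by the sample-size section, a true deficit of 0.5 would pass only about 5% of the time. To pass, the observed deficit must be below 0.5 − 1.645 × 0.164 = 0.23 at 500 per arm, which is 5/4.77 = 1.05, about 5% longer. The point therefore does not rest on slower gain at the margin; it rests on cure being a different outcome.

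**Low power for cure.** A reader might argue from the chance that a cure deficit is non-significant. The switch does not depend on any cure test, so that chance does not measure the fault.

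**The cost figures come from another trial** with an average stay of 8 weeks in both arms. If cure fell through longer stays, the 16-dollar saving (91 − 75) would shrink, and the cost analysis would show part of that. This objection stands, which is why the table is an illustration and not a forecast.

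**Conclusion.** The point holds as a mismatch of endpoints within Annex 5. The rule that licenses an equal-effect analysis is tied to weight gain, the effect that matters to the evaluation is cure, and the expected branch cannot meet the section 2.2 objective. The link from the switch to weight gain is an inference, because section 3.1 c names no endpoint, but the protocol contains no other non-inferiority hypothesis to which it could refer.

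On size, cost minimisation would be selected with probability about 0.86 to 0.92 if true velocities are equal. Under the assumptions shown, it would present a 17.6% saving where the saving per cured child is about 12% to 13%, 5% to 7% or nil, for cure deficits of 5, 10 and 15 points. Nothing in the documents says that such a deficit is likely, and the chance that weight gain is non-inferior while cure falls has not been estimated. The primary clinical conclusion is unaffected. This should be corrected, as a matter for the nested economic study.

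**What to change.** In Annex 5, section 3.1 c, remove the dependence on the non-inferiority result. State that, whatever the weight-gain result, the difference in cost per child and the difference in cure rate between arms will be estimated together with their uncertainty, and that the cost-only comparison is a secondary presentation. Then align two other places: items (b) and (c) of section 3.1 i, so that both are reported in every case, and section 3.2.2, so that the sensitivity analyses cover uncertainty in cure as well as in cost. The method for joint uncertainty can be left to the analysis plan; because unit costs come from interviews and feed a model, a patient-level bootstrap may not be available.

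An alternative that also removes the mismatch is to keep the switch but make it conditional on a pre-specified non-inferiority margin for cure.

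The cost is small. Cure by arm, cost collection and the decision tree are already planned, and the efficacy data reach the economic evaluation only after the main results, so trial conduct is untouched. The downside is a little more analysis work and a less simple headline.
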